**Figure 1 F1:**
[figure not shown]
The flow chart of randomised controlled trial.

### Monitoring

After screening, patients meeting the inclusion criteria should participate in the study as long as possible. If not, we must save the record to judge bias. Meanwhile, recording the patient’s basic information is necessary to discuss the results of the experiment.

Before the experiment, we will explain the purpose of the experiment and the importance of the experimental procedures, to obtain consent and ideal compliance. If the selected patient is unqualified, elimination will be undesirable, and the data of the patient will be substituted by the average of the group. Furthermore, loss to follow-up is inevitable; the data of these patients will also be replaced by the average.

Surgeons and data collectors will undergo training, and a preliminary experiment involving the data measurement and questionnaire will be conducted in advance. Recording the time and staff is necessary when the collector gathers the data, which will be convenient to review.

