#### Sample size calculation

We performed a power analysis to assess the required sample size to show safety with a power (1−b) of 0.8 and α of 0.05. Based on the pre-experiment and related literature,^21^ the proportion of the control group was set to 84.6%, and the proportion of intervention group was set to 95%. We performed a two independent proportions power analysis on PASS (Power Analysis and Sample Size), and the result was 132.

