### Randomisation and blinding

Patients will be randomly divided into an experimental group and a control group using a computer-generated randomisation schedule. The random sequence will be stored in a sealed opaque envelope to ensure that the patients, personnel and the outcome assessor will be blinded to the group allocation. Until the last questionnaires have been completed, the participant’s allocated intervention will be revealed by the study secretary. If a patient's condition deteriorates, the blinding experiment will be terminated, and the patient’s safety will be given the highest priority (figure 1).

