### Statistical analysis

All data will be analysed using SPSS V.19.0 software. The differences in wound incision length, operative time, intraoperative blood loss and angles between the two groups will be analysed using a two independent-sample t-test with an α of 0.05. VAS and ODI scores at preoperation, postoperation, 3 months postoperatively, 6 months postoperatively and 12 months postoperatively will be analysed using a repeated-measures analysis of variance. The times of X-ray exposure and frequency of screw penetration out of the cortex will be compared using the χ^2^ test.

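### Filling in group averages for 'unqualified' and lost patients makes the planned tests understate uncertainty, and may discard outcomes that were measured

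*Protocol article*

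**What the plan says.** The protocol article fixes two rules under Monitoring. For a selected patient who proves unqualified, "elimination will be undesirable, and the data of the patient will be substituted by the average of the group". For drop-out, "loss to follow-up is inevitable; the data of these patients will also be replaced by the average".

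The Statistical analysis section then uses standard tests. Incision length, operative time, blood loss and screw angles "will be analysed using a two independent-sample t-test with an α of 0.05". VAS and ODI scores "will be analysed using a repeated-measures analysis of variance", at five time points from before surgery to 12 months. The number of X-ray exposures and the frequency of cortical penetration go to a chi-square test. The article states no correction of the variance for filled values, and gives neither a drop-out rate nor an allowance for one.

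**The concern.** This is a stated method, not a detail left to another document. A value set to the arm mean lies exactly at the centre of the arm. It raises n and the degrees of freedom and adds nothing to the sum of squares. The tests then treat constructed values as observed patients, and their standard errors come out too small.

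Two further problems follow from the wording.

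- The rule for unqualified patients refers to the patient's data as a whole, not to missing items. If such a patient has already been randomised, operated on and measured, observed outcomes are replaced. Those would include the perioperative and screw-angle outcomes, which are primary.
- The chi-square test of screw penetration needs each unit to fall in a category. A group average is a proportion and cannot be entered as one patient's result.

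At stake are false-positive findings, mainly on VAS and ODI, and the loss of real outcomes from the comparison by allocated group.

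**Working it through.** **Inputs from the article.** The two substitution rules (Monitoring); the tests and the α of 0.05 (Statistical analysis); the visit schedule (Table 1); the sample size (Sample size calculation). **Assumed:** 1:1 allocation, two-sided tests, the fraction f of each arm that is filled, and values missing completely at random.

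**Arm size.** The article assumes that "the proportion of the control group was set to 84.6%, and the proportion of intervention group was set to 95" per cent, "with a power (1−b) of 0.8 and α of 0.05", and reports a result of 132. With pooled variance and p̄ = (0.846 + 0.95)/2 = 0.898:

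n = [1.960 × √(2 × 0.898 × 0.102) + 0.842 × √(0.846 × 0.154 + 0.95 × 0.05)]² / (0.95 − 0.846)² = (0.839 + 0.355)² / 0.010816 ≈ 131.8, which rounds up to 132.

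The figure reproduces as patients per arm. The article does not say whether it is per arm or in total, so 66 per arm was also checked.

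**Single t-test, own-arm average.** Let k = (1 − f)n be the real values per arm. The difference in means is unchanged by the filling. The reported standard error is about √[(1 − f)σ²·2/n], and the correct one is √[σ²·2/((1 − f)n)]. Their ratio is 1 − f, so

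true type I error ≈ 2 × [1 − Φ(1.96 × (1 − f))].

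The exact version uses the ratio √[((2k − 2)/(2n − 2)) × (k/n)] and t distributions. For example, with n = 132 and 13 values filled per arm, k = 119 and the ratio is √[(236/262) × (119/132)] = 0.901, giving 7.7%.

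| f per arm | Approximate | Exact, 132 per arm | Exact, 66 per arm |
|---|---|---|---|
| 5% | 6.3% | 6.3% | 6.1% |
| 10% | 7.8% | 7.7% | 8.0% |
| 20% | 11.7% | 11.6% | 11.6% |

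Simulation (50,000 trials per setting) agreed to within about 0.2 percentage points. The inflation depends on f and hardly at all on n, so neither a larger trial nor the other reading of 132 removes it.

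**Which outcomes these figures fit.** Table 1 places incision length, operative time and blood loss on day 0 and the screw angles on day 1. Later loss to follow-up cannot remove them. For these t-tests, f comes mainly from the unqualified-patient rule.

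**Repeated-measures ANOVA for VAS and ODI.** This was simulated with 132 per arm, the five stated time points, random monotone drop-out, own-arm visit means filled in, and within-patient correlation of 0.3 to 0.7 (10,000 trials per setting).

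| Lost by 3, 6 and 12 months (assumed) | Group effect | Group-by-time |
|---|---|---|
| 2%, 5%, 10% | about 6% | about 6.5% |
| 5%, 10%, 20% | about 7% | about 9% |

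The inflation is smaller than for a single t-test because the first two time points are complete and fewer values are filled at the earlier follow-up visits.

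**Pooled average.** If the average is taken over both arms, the standard error shrinks as before, but the difference between arms also shrinks towards zero. Simulated type I error then stays at 4.8% to 5.2%, and the harm is a diluted effect estimate.

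**The case against.** The strongest case against concerns reach and size, and much of it stands.

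- A reader might infer that drop-out pushes the primary t-tests to 8% or 12%. The documents do not support this. Those outcomes are complete by day 1, and nothing in the article suggests that 10% to 20% of patients will be unqualified.
- A reader might expect the worst effect at 24 months. VAS and ODI are collected then, but the stated ANOVA stops at 12 months.
- Inflation requires the own-arm average. The first rule speaks of the group, and the randomisation section defines an experimental and a control group, so this is the natural reading. The loss-to-follow-up sentence, however, says only the average.
- It is tempting to say that real data are certainly overwritten. The paragraph opens with matters before the trial, consent and compliance, and does not say that the unqualified patient has been operated on or measured. For lost patients, the ordinary reading is that only absent values are filled. Replacing observed data is therefore a conditional consequence of the first rule. The reference to a group does suggest an allocated patient.
- Bias from unequal drop-out is not specific to this rule. At a single time point, own-arm filling gives the same difference as analysing completers only.

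None of this rescues the rules. They are written as fixed procedures, and either reading of the average damages the analysis.

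**Conclusion.** The point holds. Followed as written, the plan counts constructed values as patients. With own-arm averages and values missing at random, any filling raises the type I error above 5%. For VAS and ODI to 12 months the rise is moderate: to about 6% to 7% with 10% lost, and to about 7% (group) and 9% (group-by-time) with 20% lost. For the day 0 and day 1 t-tests, the single-test figures apply only to the share of patients filled under the unqualified-patient rule, which is unknown and may be small. With a pooled average, type I error is preserved and the effect is diluted instead. The loss of observed primary outcomes depends on unqualified patients having been randomised and measured. The failure of the rule for the chi-square test of screw penetration depends on no assumed rate. All drop-out fractions above are assumptions, because the article gives none.

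**What to change.** - Delete both substitution sentences from Monitoring.
- State that every randomised patient is analysed in the allocated group with the data actually observed, including patients later found ineligible, and add a sensitivity analysis that excludes the ineligible.
- Analyse VAS and ODI with a method that uses all observed visits and fills in nothing, such as a mixed model for repeated measures.
- Multiple imputation as a sensitivity analysis is optional; correcting the defect does not require it.

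The cost is a change of wording and a different analysis procedure for VAS and ODI, with no extra patients or visits. Confidence intervals will be slightly wider, because they will reflect only the information collected.

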### Study procedure

A retrospective review of all patients will be conducted by examining their medical records before the operation. The involved segments were identified via a C-arm machine and then marked on the patient’s skin. The patients’ CT images with a thickness less than 1 mm will be exported from the Star PACS image system of the hospital and imported into the Mimics 16.0 to construct 3D images, in which we adjust the threshold depending on the bone density. We regard the two adjacent segments as a functional segmental unit (FSU), such as L2-3, L3-4, L4-5 or L5-S1.

Then, the individual 3D navigation templates will be designed and printed using CATIA software and MeditoolCreate. The detailed steps are as follows: the FSU digital data in the Mimics 16.0 will be saved in STL format and imported into CATIA software. We will establish the optimal screw trajectory, which includes two vertebral pedicle screws trajectories and one contralateral translaminar facet screw trajectory. We will measure three angles of the translaminar facet screw trajectory: α, β and γ; α is the angle between the screw trajectory and the vertical line in the anteroposterior view; β is the angle between the screw trajectory and the upper endplate of the lower vertebra in the lateral view; γ is the angle between the screw trajectory and the midline of the lumbar vertebra in the top view (figure 2). The pedicle screw trajectories will be designed according to method of Roy-Camille.^22^ We will measure two angles, δ and ε, which is the angle between the ideal screw trajectory and the midline of the lumbar vertebra in the top view, respectively (figure 2).

**Figure 2 F2:**
[figure not shown]
The designed pedicle screw trajectory and translaminar facet screw trajectory: α is the angle between the translaminar facet screw trajectory and the vertical line in the anteroposterior view; β is the angle between translaminar facet screw trajectory and the upper endplate of lower vertebra in the lateral view; γ is the angle between translaminar facet screw trajectory and midline of the lumbar vertebra in the top view; δ and ε are the angles between pedicle screw trajectory (upper vertebra and lower vertebra) and midline of the lumbar vertebra in the top view.

After the optimal screw trajectories were determined, the curved posterior surface of the lumbar vertebra around the screw entry point was extracted to create the 3D navigation template (figure 3). Then, we imported the 3D navigation template file into the 3D printer to rapid print it through MeditoolCreate (figure 4). The experiment on 3D printed lumbar model will be conducted before clinical to make sure the accurate screw trajectory (figure 5).

**Figure 3 F3:**
[figure not shown]
The designed 3D navigation template in CATIA software.

**Figure 4 F4:**
[figure not shown]
3D navigation template imported into MeditoolCreate software to print.

**Figure 5 F5:**
[figure not shown]
One example of the experiment on conducted 3D printed lumbar model before clinical application to make sure the accurate screw trajectory.

The 3D navigation template will be sterilised and used to guide the screw in further operations on the patients. In experimental group, the dissection of the paraspinal tissue will performed at one side to expose the part of spinous process, laminar and facet joint; the 3D navigation template will be attached to the surface of the above bony construction. Then, the Kirschner wire (K-wire) will be inserted inside the 3D navigation template, and a trajectory for the screw will be fashioned with a cannulated drill; screws will be subsequently introduced. In the control group, multiple X-ray fluoroscopy will be used, and the screw trajectory will be adjusted by intraoperative X-ray fluoroscopy.

After the operation, CT scans of the patients in both groups will be obtained, and the α1, β1, γ1, δ1 and ε1 angles will be measured corresponding to the angles of the optimal screw trajectory in 3D images. The placement and position of the screws will be divided into three types (type I, the screw does not penetrate out of the cortex; type II, the screw partially penetrates out of the cortex, but by less than 2 mm; and type III, the screw penetrates out of the cortex by more than 2 mm).

### Outcome measure

#### Primary outcomes (table 1)

**Table 1 T1:** The data need to collect through the research

	Baseline	Perioperation	Postoperation				
Assessment	−1 day	Day 0	Day 1	3 months	6 months	12 months	24 months
Eligibility criteria	×						
Recruitment	×						
Informed consent	×						
Randomisation	×						
Baseline demographics	×						
Medical history	×						
X-ray exposure		×					
Wound incision length		×					
Operative time		×					
Blood loss		×					
Complications		×	×	×	×	×	×
Screw angles							
α1			×				
β1			×				
γ1			×				
δ1			×				
ε1			×				
The position of the screws			×				
VAS of back pain	×		×	×	×	×	×
VAS of leg pain	×		×	×	×	×	×
ODI	×		×	×	×	×	×

ODI, Oswestry Disability Index; VAS, visual analogue scale.

Screw angles compared with the optimal screw trajectories in the 3D digital images and the position of the screws.Wound incision length, operative time, intraoperative blood loss, times of X-ray exposure and complications.

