**Methods and analysis:**

Patients who meet the criteria of the surgery will be randomly divided into experimental groups and control groups by a computer-generated randomisation schedule. We will preoperatively design an individual 3D navigation template using CATIA software and MeditoolCreate. The following primary outcomes will be collected: screw angles compared with the optimal screw trajectories in 3D digital images, length of the wound incision, operative time, intraoperative blood loss and complications. The following secondary outcomes will be collected: visual analogue scale (VAS) for back pain, VAS for leg pain and the Oswestry Disability Index. These parameters will be evaluated on day 1 and then 3, 6, 12 and 24 months postoperatively.

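### The stated alpha and power attach to no identified primary outcome: the primary list is unranked, differs between abstract and body, and the trial is sized on a proportion of an unnamed event

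*Protocol article*

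**What the plan says.** - **Primary set, body.** The first line under Primary outcomes reads "Screw angles compared with the optimal screw trajectories in the 3D digital images and the position of the screws"; the second reads "Wound incision length, operative time, intraoperative blood loss, times of X-ray exposure and complications". Neither line ranks the items. The Study procedure section and Table 1 itemise five angles: "the α1, β1, γ1, δ1 and ε1 angles will be measured corresponding to the angles of the optimal screw trajectory in 3D images".
- **Primary set, abstract.** The Methods and analysis paragraph of the abstract gives the primary outcomes as "screw angles compared with the optimal screw trajectories in 3D digital images, length of the wound incision, operative time, intraoperative blood loss and complications". Screw position and X-ray exposure are not among them.
- **Tests.** In the Statistical analysis section, incision length, operative time, blood loss and angles "will be analysed using a two independent-sample t-test with an α of 0.05". For two further outcomes: "The times of X-ray exposure and frequency of screw penetration out of the cortex will be compared using the χ^2^ test". No alpha is attached to that sentence, and complications do not appear in the section.
- **Sizing.** The Sample size calculation section says the aim is to show safety, with power 0.8 and alpha 0.05. It states that "the proportion of the control group was set to 84.6" per cent and the intervention proportion to 95%, and reports a result of 132. It does not name the event.

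**The concern.** A sample size calculation fixes alpha and power for one stated comparison. Here that comparison cannot be identified. The reader is told of two proportions but not what is counted, in what unit (patient or screw), or which listed primary outcome they belong to. Meanwhile several outcomes carry the label primary, most with their own test at 0.05, and the abstract and body disagree on which they are.

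The consequence lies in the eventual report. A significant difference in incision length, operative time or a single angle could be presented as success on a primary outcome, although the trial was sized on something else. The 0.05 and 0.8 in the plan would then not describe the error rate or the power of the conclusion drawn.

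**Working it through.** **1. The plan's own figure.** Inputs from the Sample size calculation section: p1 = 0.846, p2 = 0.95, alpha 0.05, power 0.8. Sidedness and allocation ratio are not stated; two-sided and 1:1 are assumed.

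n per arm = [1.960·√(2·p̄(1−p̄)) + 0.842·√(p1(1−p1) + p2(1−p2))]² / (p2−p1)², with p̄ = 0.898.

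- 2·0.898·0.102 = 0.1832; square root 0.428; times 1.960 = 0.839.
- 0.846·0.154 + 0.95·0.05 = 0.1778; square root 0.422; times 0.842 = 0.355.
- (0.839 + 0.355)² / 0.104² ≈ 1.425 / 0.01082 ≈ 131.8, so **132 per arm**.

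The stated 132 is thus reproduced as a per-arm figure (264 in total). The plan does not say which it is; if 132 were the total, power at 66 per arm would be about 51%. The arithmetic is sound per arm. What is missing is the event to which it applies.

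**2. Counting the primary outcomes.**

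| Outcome | Count | In abstract's primary list | Test named | Alpha written |
|---|---|---|---|---|
| Screw angles | 5 | yes | t-test | 0.05 |
| Incision length, operative time, blood loss | 3 | yes | t-test | 0.05 |
| Screw position (cortical penetration) | 1 | no | chi-square | none |
| X-ray exposure | 1 | no | chi-square | none |
| Complications | 1 | yes | none | none |

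Total: 5 + 3 + 1 + 1 + 1 = 11, or seven items if the angles are one entry.

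**3. Size of the multiplicity.** Suppose that any one significant primary result is claimed as success, that every null hypothesis is true, and that the k tests are independent at 0.05. Then P(at least one false positive) = 1 − 0.95^k.

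| Tests counted | k | Result |
|---|---|---|
| Listed items, angles as one | 7 | 30.2% |
| Explicit 0.05 | 8 | 33.7% |
| Abstract's list, angles separate | 9 | 37.0% |
| With a named test | 10 | 40.1% |
| All | 11 | 43.1% |

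The rows for 7, 9, 10 and 11 assume 0.05 where the plan writes none; those for 7, 9 and 11 also assume a test for complications.

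With equal positive correlation among eleven tests, simulation gives about 37% at correlation 0.3, 30% at 0.5 and 18% at 0.8. Under any dependence the bound is 11 × 0.05 = 55%.

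**4. Why the unit of the proportion matters.** If 84.6% and 95% were per-screw rates and the three screws in a patient were independent (an assumption), the patient-level rates for all three being satisfactory would be 0.846³ = 61% and 0.95³ = 86%. That is a different calculation from the one reported.

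**The case against.** **Eleven tests at 0.05, hence 43%.** A reader might infer this, but the plan does not say it. It writes 0.05 only for the t-tests, states no alpha for the chi-square tests and names no test for complications. Splitting the angles into five is reasonable because Table 1 does so, but the outcome and analysis lines refer to them collectively. This objection stands, and 43% is one scenario in a range.

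**The global null is implausible, and no success rule is stated.** Controls are guided by repeated fluoroscopy while the template guides the other arm, so equal X-ray exposure is hardly a realistic null. Nor does the plan say that one significant result makes the trial a success. Both points stand; the percentages are conditional on those assumptions.

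**Only screw position or complications can be the sized proportion.** This is also tempting, but the document does not establish it. The figures come from a pre-experiment and a cited source that are not shown, the stated aim is safety, and the authors put X-ray exposure under a chi-square test as well. Likewise, nothing shows that the figures are patient-level or refer to screws wholly within the cortex.

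**Multiplicity may be handled in an analysis plan that is not shown.** That is fair as to the adjustment method, whose absence here is not the point. An unseen plan would not remove the conflict between the abstract and the Primary outcomes section. Nor would it alter the fact that this document sizes the trial on an event it does not name.

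**Conclusion.** The point holds in a limited form. The document fixes an unranked primary set, gives a different set in its abstract, writes an unadjusted 0.05 for eight of the primary tests, and sizes the trial on a proportion of an unnamed event. Alpha 0.05 and power 0.8 are therefore tied to no identified primary outcome.

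The best-supported size is about 34%, for the eight tests with a written 0.05 (counting each angle as a test). It rises to 40% or 43% only if 0.05 is also assumed for the chi-square tests and, for 43%, a test is assumed for complications. All three figures require independence, all nulls true and success on any one result. Positive correlation, which is likely among angles and among perioperative measures, lowers them, but even at 0.8 the eleven-test figure is about 18%. The document does not support the claim that the trial has a 43% false-positive rate, or that a particular outcome must be the one sized. The sample size arithmetic itself is not faulted as a per-arm figure.

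**What to change.** - Name as the single primary outcome the one to which 84.6% and 95% refer. State its unit (patient or screw) and what counts as success, and say whether 132 is per arm or in total.
- Screw position is a natural candidate: it is already graded on CT in three types and already has a chi-square test. The sponsor must confirm that the two proportions refer to it and at what level; if they do not, the basis of the sample size must be restated.
- Make the remaining outcomes secondary, or test them by Holm's procedure after the primary.
- Use the same list in the abstract, the Sample size calculation, the Primary outcomes and the Statistical analysis sections.

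Naming one primary outcome keeps the planned power. Splitting alpha does not: at 0.05/11 = 0.0045, 132 per arm gives about 48% power for 84.6% against 95%, and 228 per arm would be needed.

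The cost is a change of text, and fewer outcomes can be called primary. It becomes larger only if the proportions turn out to belong to a different outcome or unit, in which case the sample size has to be recalculated.
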